### Participant timeline

Participants will attend visits at baseline (week-2 and Week 0, randomisation), Week 2, Week 4, Week 6, Week 8, Week 12 and year 1. The CPIPB infusion runs for the first 14 days (Week 0 to Week 2). Data collection points for specific outcomes are outlined in the schedule of assessments (**Table 1**).

**Table 1 T1:** Schedule for data collection, the process of the assessments per visit.

Measures	Baseline	Intervention phase					
Time(weeks)	-2-0	2	4	6	8	12	1 year
Informed consent	√						
Demographics and Past medical history	√						
Physical examination	√	√	√	√	√	√	√
Laboratory Tests	√	√				√	√
Hemodynamic Tests	√	√	√	√	√	√	√
Electrocardiogram	√						
Ascertainment of Inclusion and Exclusion Table	√						
Routine follow-up measurement table	√	√	√	√	√	√	√
Adverse events	√	√	√	√	√	√	√
Endpoint events		√	√	√	√	√	√
Treatment adherence assessment	√	√	√	√	√	√	√

Treatment adherence assessment includes compliance with CPIPB infusion (Weeks 0-2) and long-term standard of care (e.g., offloading, wound care).

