#### Follow-up data

This includes ulcer healing status, ulcer area measurements, signs of infection, pain scores, hemodynamic measurements, Wound-QoL (assessed at 12 weeks), adverse events, block-related complications, factors related to ulcer recurrence, changes in concomitant medications and treatment adherence.

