#### Secondary outcome analysis

Time-to-event outcomes (time to healing, time to recurrence) will be analysed using Kaplan-Meier curves and compared using the log-rank test. Hazard ratios (HR) with 95% CIs will be estimated using Cox proportional hazards regression, adjusting for covariates.

Continuous outcomes (e.g., percentage area reduction, change in VAS, change in TcPO2, Wound-QoL scores) will be compared using independent t-tests or Mann-Whitney U tests, depending on data distribution. Analysis of covariance (ANCOVA) may be used to adjust for baseline values.

Binary secondary outcomes (e.g., proportion achieving ≥50% area reduction, infection incidence) will be compared using chi-square or Fisher’s exact tests, with ORs and 95% CIs from logistic regression.

Adverse event rates will be summarized descriptively and compared using Fisher’s exact test.

To address missing primary and secondary outcome data, multiple imputation by chained equations (MICE) will be performed as a sensitivity analysis under the missing-at-random (MAR) assumption. No interim analysis is planned for this study due to the relatively modest sample size (n=78). To control the family-wise error rate, the Bonferroni correction will be applied to adjust p-values for multiple comparisons among secondary outcomes. All statistical tests will be two-sided with a significance level set at P < 0.05. Statistical analysis will be performed using SPSS version 18.0 (SPSS, Inc., USA) and GraphPad Prism version 8.2.

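### Repeatedly measured secondary outcomes are compared with one-value-per-patient tests, with no analysis visit or summary named and baseline adjustment only optional

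*Protocol article*

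**What the plan says.** The Participant timeline section of the protocol article sets post-baseline visits at "Week 2, Week 4, Week 6, Week 8, Week 12 and year 1". Table 1 ticks the row "Hemodynamic Tests" at every one of them, and likewise the row "Routine follow-up measurement table". The Baseline data section shows that the haemodynamic set includes TcPO2 and PSV.

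The Follow-up data section lists "ulcer area measurements, signs of infection, pain scores, hemodynamic measurements" without a time point; of the outcome measures there, only Wound-QoL is tied to 12 weeks. Table 1 has no row of its own for ulcer area or VAS, so their collection at every visit is an inference from the routine follow-up row and this list.

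Under Secondary outcome analysis, the continuous outcomes (percentage area reduction, change in VAS, change in TcPO2 and Wound-QoL are given as examples) "will be compared using independent t-tests or Mann-Whitney U tests, depending on data distribution". The next sentence adds: "Analysis of covariance (ANCOVA) may be used to adjust for baseline values". The same section applies a Bonferroni correction among secondary outcomes, sets two-sided tests at 5%, and plans multiple imputation as a sensitivity analysis. It names no analysis visit, no summary over visits and no repeated-measures model for these outcomes.

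**The concern.** The stated tests do not fit the stated schedule. A t-test, a Mann-Whitney test and an ordinary ANCOVA each need one number per patient, while perfusion alone has five readings up to Week 12. Three things remain open that could change the result:

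- **Which reading is tested.** One visit, a per-patient average, or each visit in turn all fit the text. Each visit in turn means five tests per outcome inside or outside the Bonferroni family.
- **Whether baseline is adjusted for.** This is optional, although it is where most of the precision at a fixed visit lies.
- **Who is in the main comparison.** If a single visit is analysed, a patient without that visit drops out of it even if earlier readings exist. Imputation enters only as a sensitivity analysis.

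The Discussion relies on TcPO2 and PSV as objective evidence of the proposed mechanism, and expects VAS to fall. The infusion runs only from Week 0 to Week 2, so the size of a perfusion or pain effect may differ greatly between Week 2 and Week 12. Leaving the visit open therefore affects both power and the meaning of a null result.

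**Working it through.** **The plan's own figure.** The Sample size section uses 47% against 80%, one-sided 5%, 90% power. With the pooled formula: [1.645 × √(2 × 0.635 × 0.365) + 1.282 × √(0.47 × 0.53 + 0.80 × 0.20)]² / 0.33² = (1.120 + 0.820)² / 0.1089 = 34.6, so 35 per arm. Then 35 / 0.9 = 38.9, so 39 per arm and 78 in total. This reproduces, but it concerns the binary primary endpoint. It supplies only the n for what follows.

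**Inputs.** 35 completers per arm, 10% dropout and two-sided 5% are from the document. It gives no SD or correlation. Assumed: unit SD at each visit, equal correlation ρ between all visits including baseline, and effects in SD units.

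**Formulas.** Variance per patient, v:

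- change from baseline at one visit: 2(1 − ρ)
- ANCOVA at one visit: 1 − ρ²
- baseline-adjusted mean of five visits: (1 + 4ρ)/5 − ρ²

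The standard error of the arm difference is √(2v/35). Power is from the noncentral t distribution with 68 degrees of freedom.

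**Constant 0.5 SD effect at every visit:**

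| ρ | v: change / ANCOVA / mean | Change, one visit | ANCOVA, one visit | Five-visit mean |
|---|---|---|---|---|
| 0.4 | 1.20 / 0.84 / 0.36 | 47% | 61% | 93% |
| 0.6 | 0.80 / 0.64 / 0.32 | 63.5% | 73% | 95% |
| 0.8 | 0.40 / 0.36 / 0.20 | 90% | 93% | 99.6% |

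At ρ = 0.6 the standard errors are 0.214, 0.191 and 0.135. The normal approximation gives 96% for the mean. Testing change at each visit at 0.05/5 = 0.01 has about 38% power per test at ρ = 0.6. Uncorrected, five independent tests would carry a familywise error of 1 − 0.95⁵ = 23%; correlated visits would give less.

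**What a mixed model adds at a fixed visit.** Take ρ = 0.6 and 10% lost just before Week 12. Given baseline, the Week 12 variance is 0.64. Given baseline and the four earlier visits it is 1 − 5 × 0.36/(1 + 4 × 0.6) = 0.471. So R² = 1 − 0.471/0.64 = 0.265, and the variance relative to completer ANCOVA is 1 − 0.10 × 0.265 = 0.974. Dropout spread evenly over the visits gives about 0.98. The cut is therefore about 2-3%, or roughly one point of power.

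**Effect not constant, ρ = 0.6:**

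- 0.8 SD at Week 2 and none later: a Week 2 t-test on change has ratio 0.8/0.214 = 3.74 and power about 96% (slightly higher with nearer 39 per arm present at Week 2). The five-visit mean has effect 0.8/5 = 0.16, ratio 0.16/0.135 = 1.18 and power about 22%.
- 0.2 SD remaining at Week 12: the Week 12 t-test on change has ratio 0.2/0.214 = 0.94 and power about 15%.

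**The case against.** The best defence has four parts.

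- **The text does not force readings to be thrown away.** A t-test on a per-patient mean or area under the curve would use them all and fits the wording, and an analysis plan not shown may fix it. This stands in part: a reader might infer that most follow-up readings will be discarded, but the document does not say so. What it does state is a method that needs one value per patient, without baseline adjustment as the default, and that choice is open to criticism as written.
- **The large power gain is not like for like.** A reader might infer that a repeated-measures model lifts power from about 63% to the mid-90s. That compares a single-visit contrast with an average over visits, which answers a different question. At the same visit the rise is to about 73%, and plain ANCOVA, already permitted, gives nearly all of it. This stands in full.
- **The average may be the wrong target here.** The block ends at Week 2, and an average as the only formal test could miss an effect confined to that visit. This also stands.
- **Missing data are partly covered.** The article plans imputation and a final assessment of patients who leave early. True, but the imputation is only a sensitivity analysis, so the main comparison would still omit patients without the analysed value.

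It is also fair that repeated collection is explicit only for haemodynamics.

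**Conclusion.** The point holds as a worthwhile improvement to the secondary analyses; the primary endpoint is unaffected. The named tests are valid. The weakness is that they are set against repeated measurements with neither the visit nor a summary fixed, baseline adjustment optional, and partial follow-up unused in a single-visit main comparison.

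The size is moderate: at a fixed visit, about 63% to 73% power (ρ = 0.6, 0.5 SD, 35 per arm), nearly all from baseline adjustment. Over ρ from 0.4 to 0.8 the rise is from 47% to 61% at the low end and from 90% to 93% at the high end. Power in the mid-90s needs both an average contrast and an effect sustained over Weeks 2-12. With an effect at Week 2 only, that contrast falls to about 22%. The documents support neither effect pattern over the other, so they do not support the average as the default test. All of these figures rest on an assumed SD and correlation structure.

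**What to change.** For VAS, TcPO2 and PSV, and for ulcer area on a suitable scale, make the main analysis one mixed model for repeated measures on Weeks 2, 4, 6, 8 and 12. Include arm, visit, arm-by-visit and the baseline value as covariate.

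Before unblinding, fix one contrast per outcome to enter the Bonferroni family, chosen for the question it answers. Examples are Week 2, at the end of the infusion, for perfusion and pain, or the Weeks 2-12 average if a sustained effect is the question. Report the other visit-specific differences from the same model descriptively. Wound-QoL, with one follow-up value, can keep a single-visit comparison. State explicitly at which visits ulcer area and VAS are recorded.

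The cost is analysis wording: no new visits, data or patients. The downsides are a covariance assumption, the need to commit to a contrast in advance, and, for ulcer area, a possible change of scale from percentage reduction.

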Regional anaesthesia techniques targeting the lower limb may offer benefits beyond analgesia by modulating sympathetic tone and improving perfusion. Ultrasound-guided continuous parasacral ischial plane block (CPIPB) is a novel technique for continuous sacral plexus blockade. Our prior research standardized the CPIPB catheter placement procedure, confirming its feasibility and safety (17). We observed that CPIPB provides effective lower limb analgesia and appears to improve circulation via vasodilation, likely through blockade of sacral plexus and sacral sympathetic nerves (18). Subsequent preclinical work suggested that CPIPB promotes wound angiogenesis following sympathetic blockade, thereby accelerating DFU healing (19).

Given these preliminary findings, this clinical trial aims to determine whether CPIPB, as an adjunct to standard of care (SOC), can clinically accelerate the healing of chronic, non-healing DFU compared to SOC alone. We will conduct a randomised parallel-controlled trial to determine the impact of CPIPB on patients with DFU. We hypothesize that CPIPB would significantly improve ulcer healing without provoking significant adverse reactions compared to SOC. In addition, these findings potentially pave the way for a safe and effective adjunctive therapy for DFU.

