### Harms

Adverse events (AEs) and serious adverse events (SAEs) will be proactively monitored and recorded throughout the study. Daily clinical inspection of the catheter site will be conducted; if infection is suspected, the catheter will be removed immediately for tip culture, and empirical antibiotics initiated (26). To prevent Local Anaesthetic Systemic Toxicity (LAST), staff and patients will be educated on early symptoms, and 20% lipid emulsion will be kept readily available in the ward following ASRA guidelines (27). Catheters will be removed at protocol completion (Day 14) or earlier in the event of local infection, dislocation, severe pain, patient request, or suspected LAST. Participants will undergo routine ward surveillance and continuous vital-sign monitoring, with immediate unscheduled assessments triggered by any new symptoms. A 24-hour communication pathway is established between the clinical teams; in case of serious complications, the infusion will be stopped immediately and resuscitation initiated. All AEs will be assessed for severity and causality, and SAEs will be reported to the Ethics Committee within established timelines.

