#### Hemodynamic safety monitoring and management

Vital signs will be monitored continuously during catheterization, every 4 hours for the first 24 hours in the ward, and twice daily at home. If significant hypotension (systolic blood pressure <90 mmHg or >20% reduction from baseline) or bradycardia (heart rate <50 bpm) occurs, the infusion will be paused, the research team will be notified, and standard resuscitation (fluids, ephedrine, or atropine) will be initiated. Concurrently, the patient will be evaluated for LAST; if suspected, the institutional lipid rescue protocol (20% lipid emulsion) will be activated immediately. In such cases, the intervention will be permanently discontinued, the catheter will be removed, and the participant will be withdrawn from the trial with a two-week safety follow-up.

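### The between-arm Fisher comparison of adverse event rates does not allow for the extra safety checks that the catheter brings to the CPIPB arm

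*Protocol article*

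**What the plan says.** The analysis rule is in Secondary outcome analysis: "Adverse event rates will be summarized descriptively and compared using Fisher’s exact test". The same section adds: "All statistical tests will be two-sided with a significance level set at P < 0.05". Nothing there limits the comparison to particular kinds of event.

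The Introduction makes relative safety part of the hypothesis: "We hypothesize that CPIPB would significantly improve ulcer healing without provoking significant adverse reactions compared to SOC". Secondary outcomes lists adverse events among the end points.

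Collection is described in three places.

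- **Harms** opens in general terms, "Adverse events (AEs) and serious adverse events (SAEs) will be proactively monitored and recorded throughout the study", then turns to the catheter: "Daily clinical inspection of the catheter site will be conducted". It also provides for teaching staff and patients the early symptoms of local anaesthetic toxicity.
- **Hemodynamic safety monitoring and management** says "Vital signs will be monitored continuously during catheterization, every 4 hours for the first 24 hours in the ward, and twice daily at home". It sets blood pressure and heart rate limits at which the infusion is paused.
- **Participant timeline, Table 1** collects adverse events in both arms at baseline, Weeks 2, 4, 6, 8 and 12, and 1 year.

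For the SOC arm, the Control group section gives weekly debridement as indicated, dressing changes every 2 to 3 days (daily if needed) and scheduled wound visits. CPIPB patients receive this care as well.

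**The concern.** A comparison of adverse event proportions measures harm only if an event of a given kind is equally likely to be found and recorded in either arm. Here the catheter brings a layer of observation that SOC patients have no evident reason to receive. Events that appear only when someone looks, such as a symptomless low blood pressure, a slow pulse or a minor symptom the patient has been taught to report, will be found more often in CPIPB even if they occur equally often. Catheter dislocation, catheter-site infection and local anaesthetic toxicity cannot occur in SOC at all, so testing them partly tests whether a catheter was placed.

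At stake is the safety half of the hypothesis. If the test shows an excess in CPIPB, the reader cannot tell harm from monitoring. The trial is open-label and most clinical assessments are unblinded, so nothing else in the design evens out detection. That the distortion runs against CPIPB makes it conservative for a claim of safety, but it does not make the estimate interpretable.

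**Working it through.** **1. The plan's own figure.** No adverse event rate or power for safety is stated. The only figure used below is 39 per group, and it reproduces. With healing rates 0.47 and 0.80 (mean 0.635), one-sided 0.05 and 90% power:

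n = [1.645 × √(2 × 0.635 × 0.365) + 1.282 × √(0.47 × 0.53 + 0.80 × 0.20)]² / 0.33² = 34.5, so 35 per group; 35 / 0.90 = 38.9, so 39 per group and 78 in total.

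**2. Scheduled checks in the first 14 days.** This assumes that home readings continue to day 14, since the article gives no end date for them.

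| | CPIPB | SOC |
|---|---|---|
| Vital signs after placement | 24/4 + 13 × 2 = 6 + 26 = 32 | none stated |
| Catheter-site inspections | about 14 | not applicable |
| Education on toxicity symptoms | yes | no evident reason for it |
| Debridement and dressing contacts | yes | yes |
| Common visit with adverse event collection | Week 2 | Week 2 |

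The rows shared by both arms do not remove the excess. From Week 2 onward the Table 1 schedule is the same in both arms.

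**3. Catheter-only events, with no assumption about detection.** With 39 per arm and none possible in SOC, the two-sided Fisher p-value for k patients with such an event is 2 × C(39,k)/C(78,k). For k = 5 it is 0.055 and for k = 6 it is 0.025. So six patients with any catheter event would by themselves give nominal significance if these events were counted in the tested rate.

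**4. Unequal detection, as an illustration.** The article gives no detection probabilities or event risks, so both are assumed. The true risk is the same in both arms (20% to 50%). The table gives the exact rejection probability of the two-sided Fisher test at 0.05 with 39 per arm.

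| Detected, CPIPB / SOC | Apparent risk ratio | Rejection probability |
|---|---|---|
| 90% / 90% | 1.0 | about 0.03 |
| 90% / 70% | 0.9/0.7 = 1.29 | 0.043 to 0.099 |
| 90% / 50% | 0.9/0.5 = 1.8 | 0.105 to 0.362 |
| 90% / 30% | 0.9/0.3 = 3.0 | 0.247 to 0.778 |

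**5. Repeated readings, also an illustration.** Suppose each reading crosses a limit by chance with probability q, each crossing is recorded as an event, CPIPB has 32 readings and SOC has one. With independent readings, P(any event) = 1 − (1 − q)^32. Readings within a patient are correlated, so a beta-binomial with within-patient correlation ρ is shown too.

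| q | ρ | CPIPB patients with an event | Fisher rejects |
|---|---|---|---|
| 1% | 0 | 28% | 94% |
| 1% | 0.1 | 13% | 31% |
| 1% | 0.3 | 7% | 3% |
| 2% | 0 | 48% | over 99% |
| 2% | 0.1 | 25% | 82% |
| 2% | 0.3 | 13% | 22% |

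For independent readings with q = 0.25%, rejection is 7%. The result runs from negligible to near certain over inputs that the article does not fix. It supports a direction, not a size.

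**The case against.** **No single pooled test is specified.** A reader might infer one Fisher test of any adverse event. The article speaks of rates in the plural, Follow-up data lists block-related complications separately from adverse events, and Harms has every event graded for severity and causality. So part of the separation is already in the data collection, and a full analysis plan could complete it. This stands. What remains is that the stated rule has no restriction and, applied as written, would take in these events.

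**SOC is not unobserved before Week 2.** Debridement and dressing contacts give opportunities to report symptoms. This also stands, but CPIPB patients have the same contacts, so the difference remains.

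**The arm is not named.** Harms says "Participants will undergo routine ward surveillance and continuous vital-sign monitoring, with immediate unscheduled assessments triggered by any new symptoms". One could read this as covering both arms, so the lack of such monitoring in SOC is an inference. It is a strong one: Study setting places recruitment and follow-up in outpatient clinics, the surrounding rules concern the catheter or infusion, and an SOC patient has no catheterisation from which a 24-hour ward period could start.

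**The thresholds are management triggers.** The blood pressure and heart rate limits say when to act on the infusion. The article does not say that one isolated reading is recorded as an adverse event. A reader might therefore take 28% or 48% of CPIPB patients as the expected false count. The document does not support that: the crossing rate has no source in it, independent readings are implausible, and the recording rule is assumed.

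**The consequence is bounded.** Adverse events are secondary, the imbalance covers 14 days, and the planned Bonferroni correction, if it covers adverse events, makes a false excess less likely. All true. A correction for multiplicity does not, however, remove a bias in the estimate.

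**Catheter and monitoring-detected events are real harms of an add-on strategy.** Removing them from view could hide what the monitoring exists to find. This stands and shapes the fix.

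**Conclusion.** The point holds. The planned comparison cannot separate harm from closer observation for events that the catheter-related checks reveal in the first 14 days, and it is uninformative for events that need a catheter. Extra detection pushes against CPIPB. One rule partly offsets this: withdrawal with a two-week safety follow-up, after the events for which the Hemodynamic section requires it, shortens later observation in CPIPB.

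The size cannot be derived from the document. The illustrations span no visible effect to a dominant one and rest on assumed detection, crossing and correlation values. Serious adverse events, amputation and events after Week 2 are little affected, and the primary endpoint is not touched.

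The conclusion rests on reading the extra checks as CPIPB only. Two stronger conclusions do not follow: that Fisher's test is the fault (any test of raw proportions would share the problem), or that the monitoring should change. The monitoring serves safety, and the remedy lies in analysis and reporting.

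**What to change.** In Secondary outcome analysis, replace the adverse event sentence with a rule along these lines:

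1. Base the between-arm test on events ascertained alike in both arms: events elicited with the same questions at the common visits (Weeks 2, 4, 6, 8, 12 and 1 year), serious adverse events, infection of the index ulcer, and amputation. Give risk differences with 95% CIs. Infection must mean the index ulcer, because catheter-site infection is looked for in CPIPB only.
2. Tabulate catheter- and block-related events for CPIPB, without a test.
3. Still report all adverse events descriptively by arm, including those found only by the extra monitoring, each flagged by how it was found, so that real harms of the add-on strategy stay visible.
4. State in the text which arm each check in Harms and Hemodynamic safety monitoring applies to, and acknowledge the difference in ascertainment when interpreting safety.

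The cost is a change of analysis wording, one added field on the adverse event form for how the event was found, and fewer events in the test, hence less precision. Common questions do not remove reporting differences that come from patients knowing their allocation. Neither the monitoring nor the sample size changes.
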